#### Secondary outcomes

##### Secondary outcome 1

Comparative predictive ability of models incorporating MRI severity scores (MEGS, sMaRIA and LI) when compared with a baseline model of standard characteristics alone, for predicting Montreal B2/B3 disease or Liège severe disease in newly diagnosed patients by 5 years.

Modelling will be conducted as for the primary outcome. Models will only be developed if the number of events/non-events is adequate; if this is not achieved, only descriptive statistics will be provided.

##### Secondary outcome 2

Identification of the best combination of individual MRE features for prediction of disabling CD (all definitions) within 5 years of new diagnosis. PCA will be used to combine multiple MRE parameters into a small number of Eigenscore variables. This allows a larger number of features to be combined without compromising statistical power. The most influential imaging features will be identified for further simplification of MRE variables included in modelling. Methods will be as in the primary outcome, and the statistical significance of including MRE features will be evaluated based on improvement of model fit (BIC) in comparison to the standard model, with additional model performance reported as appropriate.

##### Secondary outcome 3

Average per-patient and national healthcare cumulative costs incurred within 5 years of newly diagnosed CD. Hospital healthcare usage from health economic case report forms (CRFs) will be multiplied by unit costs for relevant items, summed across the 5-year follow-up period, and averaged across the study population (median and mean). Mean costs per patient will be multiplied by the estimated number of CD patients in the UK, stratifying by the presence or absence of disabling disease, to estimate the cost-of-illness following a UK diagnosis (both by UK incidence and prevalence).

##### Secondary outcome 4

Patient, disease phenotype and imaging characteristics associated with higher economic costs, within 5 years of diagnosis. Unadjusted annual and 5-year costs will be calculated separately according to the presence or absence of disabling CD, Liège and Montreal criteria, MRE parameters, treatments received and patient demographics. Comparison between groups will be by one-way analysis of variance and Mann-Whitney two-sample tests. Multivariable regression will be used to identify factors (CD status, MRE parameters, treatments received and patient characteristics) associated with higher costs. To account for skewed cost data, we will use a generalised linear model with gamma family and log link, experimenting with other distributional assumptions (log-normal, Gaussian, inverse Gaussian and negative binomial distributions), selecting the best fit as judged by residual plots and the Akaike Information Criterion. A restricted version of the model will also be applied, only using data that are available at, and soon after, diagnosis.

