#### Secondary objectives

To improve the prediction of disease phenotype within 5 years, defined by the Montreal behaviour criteria, by developing and internally evaluating a ‘baseline’ multivariable prediction model comprising standard clinicopathological variables.To identify specific combinations of individual MRE findings that best predict disabling CD within 5 years of diagnosis.To estimate the healthcare costs incurred within 5 years of a new diagnosis of CD and to explore patient, imaging and disease characteristics driving higher health economic costs.Assuming promising predictive potential, to then generate a research design for a subsequent prospective study to externally evaluate our MRE-based prediction model if appropriate.

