#### Secondary outcomes

Comparative predictive ability of prognostic models incorporating MRE severity scores (MEGS, sMaRIA and Lémann index) versus models using standard characteristics alone to predict the development of Montreal B2 / B3 disease or Liège severe disease at 5 year follow-up.Identification of the best combination of individual MRE features to predict disabling CD within 5 years of new diagnosis.Average per-patient and national healthcare costs incurred within 5 years of new diagnosis.Patient, disease phenotype and imaging characteristics associated with higher economic costs within 5 years of diagnosis.

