#### Identification of the most important MRE variables for model inclusion

Principal component analysis (PCA) will be used to reduce the number of individual MRE variables to ideally two or three eigenvector variables, for subsequent addition to the baseline clinical model. This will facilitate our ability to determine the effect on model fit of adding MRE variables.

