We believe this is the first study to investigate MRI as a predictive biomarker for development of disabling disease in newly diagnosed CD. In a dual-centre prospective study of 142 CD patients, Fiorino *et al* evaluated the predictive role of MRE on disease outcome and found that bowel damage on imaging was associated with increased future hospitalisation and surgery.^27^ However, patients were eligible if imaging was acquired within 2 years of a potential diagnosis of CD, so was not representative of a newly diagnosed cohort. A single-centre study enrolled 112 patients with relapsed CD (rather than new diagnoses) and conducted both MRE and colonoscopy.^26^ Future surgical resection was related to the presence and degree of established bowel damage (stricture, fistula or abscess) rather than the degree of inflammation. Most recently, a single-centre study of 52 patients with CD (not stratified by new diagnosis/suspected relapse) found that the presence of restricted diffusion, increased upstream dilatation from a stricture, complex fistula, perienteric inflammation, fibrofatty proliferation and increased length of disease involvement on outpatient MRE were significantly more common in patients progressing to surgery.^45^ It is unknown if these findings can be extrapolated to new diagnoses, who, by definition, are earlier in their disease trajectory than those with relapsed, established CD.^26^ Nevertheless, these studies suggest that the degree of established bowel damage may predict future adverse outcomes, rather than the degree of inflammation encountered during a flare. Unlike other biomarkers such as CRP and calprotectin, MRE has the advantage of being able to quantify both bowl damage and inflammation simultaneously.

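### Secondary outcome 2 promises the best predictive combination of MRE features, but the only combining method it names, PCA, forms its components without the outcome

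*Protocol article*

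**What the plan says.** The aim is defined by the outcome. Secondary objectives: "To identify specific combinations of individual MRE findings that best predict disabling CD within 5 years of diagnosis". The list of secondary outcomes repeats it: "Identification of the best combination of individual MRE features to predict disabling CD within 5 years of new diagnosis". The statistical methods for Secondary outcome 2 extend it to all definitions of disabling CD.

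One method is named for getting from many features to few. The section on identifying the most important MRE variables states: "Principal component analysis (PCA) will be used to reduce the number of individual MRE variables to ideally two or three eigenvector variables". The components are then added to the baseline clinical model. Secondary outcome 2 repeats the PCA step, "PCA will be used to combine multiple MRE parameters into a small number of Eigenscore variables", and gives its reason: "This allows a larger number of features to be combined without compromising statistical power". The next sentence is "The most influential imaging features will be identified for further simplification of MRE variables included in modelling", which does not say what influence is measured against. Methods otherwise follow the primary outcome, and the value of including MRE is judged by BIC against the standard model.

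**The concern.** The aim asks which features predict, whereas PCA answers which features vary together. If the analysis is run as described, a reader of the results could take the high-loading features to be the best predictors of disabling CD, although nothing in their selection tested that. Conversely, a feature that predicts well but shares little variance with the rest may get little weight in the retained components, and the study could report that MRE features add nothing. The article gives some reason to care: its Discussion says earlier studies suggest that "the degree of established bowel damage may predict future adverse outcomes, rather than the degree of inflammation encountered during a flare". Features of established damage may well be rarer and less intercorrelated than graded inflammation items, though the article gives no correlations.

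**Working it through.** **1. The plan's figures.** The protocol assumes 207 participants and 55%–60% prevalence. Events: 207 × 0.55 = 113.9 and 207 × 0.60 = 124.2. Non-events: 93.2 and 82.8. These reproduce the stated 114–124 and 83–93.

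**2. Where the outcome enters.** Let Z be the standardised MRE features (n patients, p features) and y the outcome.
- PCA: V holds the first k eigenvectors of the correlation matrix of Z. y is not an input, so V is identical for every outcome definition on the same scans.
- Components: T = ZV, with k = 2 or 3.
- Outcome model: logit P(y = 1) = standard predictors + Tγ. Here γ is fitted to y.
- Implied feature weights: Vγ. They change with the outcome, but only inside the k-dimensional space that V fixed beforehand. With 12 features (an assumption; the article gives no count), 10 or 9 directions are excluded in advance.

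**3. What BIC decides.** Adding k components improves BIC when the likelihood-ratio gain exceeds k × ln n.
- k = 2: 2 × ln 207 = 10.67, equivalent to p of about 0.005.
- k = 3: 3 × ln 207 = 16.00, p of about 0.001.

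This compares the standard model with and without the retained MRE variables. It does not compare rival combinations of features.

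**4. First simulation.** All inputs except n are assumed or chosen within the plan's range: n = 207; prevalence about 57%; 12 features, in two blocks of five with correlation 0.6 plus two unshared features; two components; no clinical covariates; 1,000 runs.

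| Where the signal lies | BIC improved | AUC in new data | Attainable AUC |
|---|---|---|---|
| Nowhere | 0.7% | 0.50 | 0.50 |
| One correlated block (log odds 0.25 per feature) | 100% | 0.74 | 0.74 |
| One unshared feature (log odds 1.0) | 0.8% | 0.50 | 0.74 |

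In the third row the predictive feature was never among the four highest-loading. The mean absolute cosine between feature weights fitted to the real and to a permuted outcome was about 0.63, where 1.0 would mean identical weights. Two random directions in a plane average 2/π = 0.64, so within the retained plane the outcome does determine the combination.

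The third row depends on stopping at two components. The leading population eigenvalues are 1 + 4 × 0.6 = 3.4 (twice), then 1 (twice, the unshared features), then 1 − 0.6 = 0.4. A third component would fall on the unshared features.

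**5. Second simulation, closer to the Discussion.** Assumed: 207 patients; nine inflammation items with pairwise correlation 0.3–0.5; three damage items with prevalence 6–12%; odds ratio 4 for any damage; no inflammation effect.
- A damage item led the first component in 0% of runs and the second in 100%.
- Adding the components improved BIC in 17–26% of runs, or 36–56% if the damage items were themselves correlated. With no effect it was about 1% or fewer.
- Ranking features by association with the outcome put a damage item first in 79–87%.
- The c-index in new patients was 0.56–0.58 for the components and 0.60 for ridge regression on the same features. With inflammation as the driver, the components were slightly ahead (0.71 v 0.70; 0.74 v 0.73).

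**The case against.** A reader might infer that Secondary outcome 2 never uses the outcome, or that it names the same best predictors whether or not anything predicts. The document does not support this. Only the PCA step ignores the outcome. The component coefficients are fitted to disabling CD, and a set of null features would normally fail BIC.

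A reader might also infer that the most influential features means those with the highest loadings. That is a natural reading, since the sentence follows the PCA sentences directly, but the criterion is not stated and the analysis plan, which is not shown, may define it.

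Nor can one infer that PCA will hide damage features. In the second simulation they led the second component, which the plan would keep. The Discussion also says it is unknown whether the earlier findings carry over to new diagnoses, and it lists perienteric inflammation and disease length among the features associated with surgery. Damage is assessed separately through the Lémann Index in the primary analysis, and the standard model already contains stricturing and perianal disease, which the simulations omit.

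Finally, outcome-blind reduction is a recognised protection against overfitting with 83–93 non-events, and where the features that vary together are also those that predict, it costs nothing.

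All of this stands. It limits the size of the problem and justifies keeping PCA. It does not close the gap between aim and method: fitting and testing two or three preformed components is not a search for the best predictive combination. This is also not a detail left to the analysis plan, because the protocol itself ties this method to this objective.

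**Conclusion.** The point holds in limited form. As written, the plan can test whether the main directions of MRE variation improve prediction of disabling CD. It cannot identify which combination of individual features predicts best, because the candidate combinations are fixed before the outcome is seen and BIC does not compare alternatives. That conclusion is structural and rests on no assumed numbers.

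The practical loss does depend on assumptions: the correlations among features, the number of components kept, and where the signal lies. It ranges from none (signal in a correlated block, AUC 0.74 of 0.74) to total (one unshared feature with two components, AUC 0.50 of 0.74). The damage scenario lies between, with a c-index deficit against ridge of 0.02–0.04. Neither simulation adjusted for the standard predictors. The matter concerns a secondary outcome and leaves the primary comparison untouched. It should be changed because it affects what the study may claim.

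**What to change.** Keep PCA as data reduction and BIC as the test of added value. Then do one of the following.

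1. **Support the claim.** Add a penalised regression that selects (elastic net or lasso) of disabling CD on the individual MRE features, jointly with the standard predictors. Ridge is unsuitable because it retains every feature. Choose the penalty by cross-validation, repeat the whole procedure in each of the planned 200 or more bootstrap samples, and report how often each feature is retained. Do this only for outcome definitions with enough events. The protocol expects about 41 Liège events (207 × 0.20 = 41.4) and makes that endpoint descriptive unless more accumulate.
2. **Narrow the claim.** Restate the objective and outcome as testing whether PCA summaries of MRE features add prediction to the standard model, and drop the claim to identify the best predictive features.

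In either case, state what the most influential features are influential on. The cost is revised wording and, for the first option, some computing; no new data are needed. The drawback of the first option is that the selected set will be unstable with 83–93 non-events. The retention frequencies will show this, and the result should be reported as exploratory.

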#### Additional retrospective cohort: inclusion criteria

The retrospective cohort will be added to METRIC accruals to achieve the required sample size.

Inclusion criteria for the retrospective cohort are as follows:

Patients aged 16 years or more with newly diagnosed CD, based on endoscopic, histological, clinical and radiological findings.MRE acquired according to METRIC standard minimum sequence data set, and performed either <3 months before or after diagnosis.Normal institutional practice is to perform MRE in all new diagnoses of CD.At least 4 years clinical follow-up data available.

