### Assessment of disease severity at follow-up

#### Time point of follow-up

Follow-up will be for a minimum of 4 years: since participants were recruited to METRIC over 30 months, this corresponds to an average follow-up of approximately 5.5 years. This provides sufficient time for clinically relevant complications of CD to manifest.^35–37^

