### Retention

Participants need not undergo additional testing to enter this study. Only data obtained during routine clinical care are necessary to both define disabling disease and provide variables for model inclusion. Where participants are lost to local follow-up, participants’ general practitioner will be contacted to obtain routine clinical information, post consent (this is only applicable to METRIC cohort and those patients on retrospective cohort who have provided consent).

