#### Health economic analysis

To estimate mean 5-year costs per patient, we require NHS hospital resource use data for all patients accumulated during the follow-up period. These will be collected in a similar manner to the METRIC study, which captured similar costs but only for a 6-month time horizon. A study-specific CRF will capture hospital resource use data for the following cost components for each patient during follow-up: all imaging investigations; endoscopy; surgery; outpatient visits; inpatient stays; day cases and medications. These will be populated at each site by the relevant research team. Unit costs will be obtained from standard published sources, including NHS tariffs.

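### Five-year costs are summed and averaged over all patients although only four years of follow-up are required, so the stated rule understates mean cost for anyone seen for less than five years

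*Protocol article*

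**What the plan says.** **Estimator.** Secondary outcome 3, under Statistical methods, multiplies hospital use by unit costs. The result is "summed across the 5-year follow-up period, and averaged across the study population (median and mean"). The mean is then scaled to UK patient numbers, split by disabling disease, to give a cost of illness. Secondary outcome 4 compares annual and 5-year costs between groups without adjustment and fits a generalised linear model (gamma family, log link) to find cost drivers.

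**Data.** The Health economic analysis section says that "we require NHS hospital resource use data for all patients accumulated during the follow-up period". Of the case report forms it says: "These will be populated at each site by the relevant research team".

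**Follow-up.** Time point of follow-up states: "Follow-up will be for a minimum of 4 years". It adds that "participants were recruited to METRIC over 30 months" and that "this corresponds to an average follow-up of approximately 5.5 years". The Study design section sets the same 4-year floor for METRIC patients. For the retrospective cohort the inclusion criterion is "At least 4 years clinical follow-up data available".

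**Recovery of lost patients.** The Retention section has the general practitioner (GP) supply routine clinical information for patients lost locally, after consent. It limits this route: "this is only applicable to METRIC cohort and those patients on retrospective cohort who have provided consent".

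**The concern.** The cost horizon is 5 years and the guaranteed observation is 4. A patient can satisfy every follow-up requirement and still have up to a year of the cost window unseen, with nobody lost. The stated rule adds up the recorded usage and divides by the whole study population. It has no term for time observed.

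Three results would be affected:

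- The mean 5-year cost per patient is too low, and the UK estimate inherits the same proportional error.
- The comparison of 5-year costs by disabling status, Liège and Montreal criteria and MRE parameters is distorted wherever the groups differ in length of observation.
- The cost regression can credit a patient or imaging feature with a difference that is only a difference in observed time.

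Care given elsewhere after a patient leaves a site would add to the shortfall, since the GP route promises clinical information and does not mention hospital resource use.

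**Working it through.** **Inputs from the protocol article**

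- 131 METRIC and 76 retrospective patients (Sample size and justification): 131 + 76 = 207, as stated.
- Minimum follow-up 4 years and METRIC recruitment over 30 months = 2.5 years (Time point of follow-up).
- Cost window 5 years (Secondary outcome 3).

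**The plan's own figure.** With uniform accrual, average METRIC follow-up is 4 + 2.5/2 = 5.25 years, against about 5.5 stated. The gap of 0.25 year is small for a figure given as approximate, but it affects the result, so both values are carried forward.

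**Step 1: METRIC shortfall with nobody lost.** Assume follow-up uniform over 4 to 6.5 years.

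- Share with under 5 years: (5 − 4)/2.5 = 40%.
- Mean shortfall among them: 0.5 year.
- Mean shortfall over all METRIC patients: 0.40 × 0.5 = 0.2 year, or 0.2/5 = 4% of the window.

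**Step 2: whole cohort.** Let x be the mean shortfall of retrospective patients, from 0 (all reach 5 years) to 1 year (all stop at exactly 4).

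Unobserved share = (131 × 0.2 + 76x)/(207 × 5)

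| x (years) | Unobserved share |
|---|---|
| 0 | 26.2/1035 = 2.5% |
| 0.5 | 64.2/1035 = 6.2% |
| 1 | 102.2/1035 = 9.9% |

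With level annual cost, these are also the percentages by which the mean is understated when the recorded sums are averaged over all 207.

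**Step 3: if METRIC follow-up averages 5.5 years.** Two uniform spreads have that mean.

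- 4.25 to 6.75 years: mean shortfall 0.75²/(2 × 2.5) = 0.1125 year; METRIC contribution 131 × 0.1125/1035 = 1.4%.
- 4 to 7 years: mean shortfall 1²/(2 × 3) = 0.167 year; METRIC contribution 131 × 0.167/1035 = 2.1%.

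The METRIC part therefore falls from 2.5% to between 1.4% and 2.1%.

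**Step 4: if costs are front-loaded.** Assume 40% of the 5-year cost falls in year 1 and 15% in each later year. Year 5 then carries 15% rather than 20%, a factor of 0.75. The understatement from Step 2 becomes 2.5% × 0.75 = 1.9% to 9.9% × 0.75 = 7.4%.

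**Step 5: transfers and losses (illustration only, since no loss rate is given).** Suppose 5%, 10% or 20% of METRIC patients are lost uniformly over the 5 years and their later care is never recorded. On average half the window is unseen, so the whole-cohort understatement is 131 × L × 0.5/207 = 1.6%, 3.2% or 6.3%. With the front-loaded profile the mean unseen share of cost is 0.40, giving 1.3%, 2.5% or 5.1%. These overlap with Step 2 in year 5 and should not simply be added to it.

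**The case against.** **The article is silent, and the detail belongs in an analysis plan that is not shown.** Handling of incomplete costs is often left to a statistical or health-economic plan, and its absence here would be no finding. A reader might infer that lost patients are entered at zero cost, but no section says so. That part of the objection stands. It does not remove the mismatch, because the article fixes a 5-year sum averaged over the study population and also fixes a 4-year minimum. Dropping incomplete patients would contradict averaging over the whole population, and multiple imputation is stated for covariates only.

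**Data may not come only from the recruiting site.** A reader might infer this from the form being completed by site teams. The text says who fills in the form and does not restrict the sources. The GP route covers METRIC participants and consented retrospective patients, and what it yields may include admissions, operations and drugs. This stands in part: the route may recover some resource use, but nothing says that it feeds the cost form.

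**Early loss hardly touches the retrospective cohort.** These patients are selected for at least 4 years of data, so apart from care at other hospitals only the fifth year is at stake. This stands.

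**The range may be too wide.** The 9.9% end needs every retrospective patient to stop at exactly 4 years. The Trial status section reports delay, with closure in late 2022 or early 2023, so actual follow-up may exceed the minimum. This also stands: if every patient reaches 5 years with complete cost data, the bias disappears.

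**Differential loss is conjecture.** A reader might infer that well patients leave while patients with disabling disease stay, which would skew the group comparisons in a known direction. The documents report no such pattern. If the leavers were the low-cost patients, the overall understatement would be smaller than the level-cost figures.

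**Conclusion.** The point holds as a mismatch between a stated estimator and the stated follow-up. Averaging a 5-year sum over all patients understates the 5-year mean whenever some are observed for less than 5 years, and the follow-up rules allow that for both cohorts.

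Under uniform METRIC follow-up of 4 to 6.5 years, level annual cost and no transfers, the understatement is 2.5% to 9.9%. It is smaller if METRIC follow-up averages the stated 5.5 years or if costs are concentrated early. Further loss through transfers is possible but cannot be sized from the documents. The direction for the overall mean and the UK figure is downward; for the group comparisons and the regression it depends on how observation time differs between groups, which is not documented.

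Severity is minor to moderate. Secondary outcomes 3 and 4 are affected; the primary prediction model is not.

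**What to change.** 1. Record for each patient the date to which hospital resource use is complete, separately from the date of the clinical outcome assessment.
2. Estimate mean 5-year cost from the annual costs already planned under Secondary outcome 4, using a censored-cost method. One example is the partitioned estimator with inverse-probability-of-censoring weights, with time after death counted as true zero cost. Carry this mean into the UK calculation.
3. Use the same weights in the 5-year group comparisons and the cost regression. Do not substitute cost per observed year: if costs fall after diagnosis, patients with short observation would look expensive and the observation-time artefact would return in another form.
4. Report the raw 5-year sum only for patients with complete 5-year cost data, with their number.

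The weights can recover year 5 only from patients who are observed through it. The number with complete fifth-year data should therefore be shown by cohort; if few retrospective patients reach 5 years, their fifth year rests on METRIC patients, and that should be stated.

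Cost: one extra date on the case report form, slightly wider intervals and a little more analysis work.

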### Study design

METRIC (Magnetic Resonance Enterography or Ultrasound In Crohn’s Disease) was a multicentre, prospective trial performed in eight National Health Service (NHS) centres across England and Scotland designed to compare the diagnostic accuracy of MRE and ultrasound (US) for the location and extent of CD.^15 28^ Consenting adult patients presenting with either newly diagnosed CD or presenting with suspected relapse were recruited: all underwent both MRE and US. Patients were followed up for 6 months minimum. In this study, we will draw solely on the group of patients who were recruited into METRIC with a new diagnosis of CD (ie, the ‘relapse cohort’ will be excluded). We will extend follow-up for the new diagnosis cohort to a minimum of 4 years.^15^ To achieve an adequate sample size, we will supplement newly diagnosed patients from METRIC (n=133) with a carefully matched retrospectively identified group of patients also newly diagnosed with CD, who did not participate in the METRIC trial.

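### The prevalence-based national cost applies first-5-year costs to patients beyond year 5, and so rests on an unstated assumption that the study cannot check

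*Protocol article*

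**What the plan says.** The Outcomes section names the outcome as "Average per-patient and national healthcare costs incurred within 5 years of new diagnosis". Under Statistical methods, Secondary outcome 3, hospital resource use is costed, "summed across the 5-year follow-up period, and averaged across the study population (median and mean"). The next step is the scaling to the UK: "Mean costs per patient will be multiplied by the estimated number of CD patients in the UK". A single stratifier is named for this step, in the words "stratifying by the presence or absence of disabling disease". The purpose given for the whole calculation is "to estimate the cost-of-illness following a UK diagnosis (both by UK incidence and prevalence").

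The costs come from newly diagnosed patients only. Study design says "we will draw solely on the group of patients who were recruited into METRIC with a new diagnosis of CD" and excludes the relapse cohort; the added retrospective cohort is also newly diagnosed. On observation time, the article says "Follow-up will be for a minimum of 4 years", with an average of about 5.5 years.

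**The concern.** The quantity being scaled belongs to a defined phase, the first 5 years after diagnosis. An annual incidence count matches that phase. A prevalence count does not, because it includes people diagnosed at any time in the past. The text does not limit the count to recent diagnoses, does not weight by time since diagnosis, and gives no cost assumption for later years. The only stratifier is disabling disease.

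The national cost is a named secondary outcome. Followed as written, the plan would put a prevalence-based UK figure next to the incidence-based one with the same apparent authority, although the study's data support only the latter. The primary prediction analysis, the per-patient costs and the cost-driver models are not affected.

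**Working it through.** **Plan's own figure.** There is none to reproduce. The article gives no UK incidence, UK prevalence, unit cost or national total. The check is therefore of form, with size shown over assumed ranges.

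**Notation.** I = UK annual new cases; P = UK prevalent cases; D = P/I; C = mean cumulative cost over years 0-5 (the study's estimate); s = share of prevalent patients within 5 years of diagnosis; r = mean annual cost after year 5 divided by mean annual cost in years 0-5. D and r are assumptions. The population is taken to be in steady state.

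**1. Incidence product, I × C.** Each new case incurs C on average over its first 5 years. The product is the 5-year cost of one annual cohort, which fits the outcome.

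**2. Prevalence product against the stated outcome.** Only patients within 5 years of diagnosis fall inside the outcome's horizon. With a fixed disease duration there are 5 × I of them, so s = 5/D and the count is too large by P/(5 × I) = D/5.

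| D (assumed) | s = 5/D | patients counted / patients in horizon |
|---|---|---|
| 15 | 33% | 3 |
| 20 | 25% | 4 |
| 40 | 12.5% | 8 |

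With exponentially distributed duration, s = 1 − exp(−5/D), which is 28%, 22% and 12%. The ratio 1/s is then about 3.5, 4.5 and 8.5.

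**3. Prevalence product as a 5-year cost of all prevalent patients.** The true cost is P × C × [s + (1 − s) × r], so planned/true = 1/[s + (1 − s) × r]. At D = 20, s = 0.25:

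| r (assumed) | s + (1 − s) × r | planned / true |
|---|---|---|
| 0.50 | 0.25 + 0.375 = 0.625 | 1.60 |
| 0.75 | 0.25 + 0.5625 = 0.8125 | 1.23 |
| 1.00 | 1.000 | 1.00 |
| 1.25 | 0.25 + 0.9375 = 1.1875 | 0.84 |

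At r = 0.5 the ratio is 1.50 for D = 15 and 1.78 for D = 40. At r = 1.25 it is 0.86 and 0.82. The sign of the error depends on r alone; D changes only its size.

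**4. Can the study inform r?** No. All participants enter at diagnosis, the established-disease cohort is excluded, and follow-up averages about 5.5 years. Little time after year 5 is seen, and the outcome does not use it.

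**5. Does the disabling stratifier repair the mismatch?** No. The Assumptions section puts disabling disease at 16% at 1 year and 58% at 5 years, so the proportion itself depends on time since diagnosis. A split taken at 5 years need not hold in a population of mixed duration, and costs after year 5 are unobserved in either stratum. The Discussion itself describes new diagnoses as earlier in the disease course than relapsed, established disease, and says it is unknown whether findings in other Crohn's populations carry over to them. The prevalence product makes the reverse transfer.

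**The case against.** The strongest reply is that the sentence can be read more kindly. The outcome is bounded to 5 years from diagnosis, so the prevalence count might mean patients within that window. Annual costs are also planned, and a condensed article may leave the sourcing of the count to a fuller economic plan. The first part does not stand, because the text refers to the number of UK patients with the disease and does not restrict it. The annual costs belong to the group comparisons of secondary outcome 4 and are not tied to the national scaling. Nor is the point about missing detail: the article states the multiplication and names prevalence as a basis.

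Four stronger readings are tempting, and the documents do not support them.

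- **The prevalence figure must be wrong, and too high.** As a cost of all prevalent patients it is exactly right if later annual costs equal early ones, and too low if they are higher. Nothing in the article shows costs falling after year 5.
- **Most prevalent patients are beyond year 5.** This needs a mean disease duration above 10 years (fixed) or about 7.2 years (exponential, 5/ln 2). It is plausible for a chronic disease, but the article does not give it. The concern does not depend on it, since any patient beyond year 5 is outside the horizon.
- **The figure is a further 5 times too large as an annual burden.** The plan describes the cost as cumulative over 5 years and never as annual.
- **The figure passes for total healthcare cost.** The hospital scope is already stated, both in Secondary outcome 3 and under Health economic analysis: "we require NHS hospital resource use data for all patients accumulated during the follow-up period".

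It also stands that only one of two national estimates is affected, and that this is a descriptive secondary outcome.

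**Conclusion.** The concern holds in a limited form. The incidence-based estimate is sound. The prevalence-based estimate goes beyond the outcome's horizon and depends on an unstated assumption of equal annual costs, and an equal disabling split, before and after year 5.

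Measured against the stated outcome, it counts about 3 to 8 times too many patients if prevalence is 15 to 40 times annual incidence. That ratio is an assumption, as is the steady state. Measured as a 5-year cost of all prevalent patients, neither the size nor the direction of the error can be settled from the documents. At a ratio of 20 the planned figure runs from 1.60 times the true value (later costs 50% of early) through correct (equal) to 0.84 of it (125%). The plan should be changed on this point, but the primary objective does not depend on it.

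**What to change.** Amend the scaling sentence in Secondary outcome 3:

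- Keep annual UK incident cases × mean 5-year cost, described as the 5-year cost of one annual diagnosis cohort.
- Replace the prevalence product with the sum, over years 0-5 since diagnosis, of mean cost in that year × estimated UK patients in that year. Label it as the cost for patients within 5 years of diagnosis. It is a one-year figure, so each of the two estimates should carry its period. As a check, with constant incidence and no losses the sum is I × (c1 + … + c5) = I × C, where c1 to c5 are the mean costs in each year, so the two totals should then agree.
- If a figure for all prevalent patients is kept, present it only as a scenario, with the assumption for costs after year 5 stated and a sensitivity range that includes later costs below, equal to and above early ones.

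No new patient data are needed, provided the resource use already collected is costed by year. The counts by year since diagnosis must come from an external source or from recent annual incidence. The price is a national figure of narrower scope.
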